### Study Design and Data Protection

This study is a case-controlled study with a case group and a control group to identify the best target population for measuring speech patterns with the VoiceSense app. We adhered to the Consolidated Standards of Reporting Trials (CONSORT) guidelines in the design of the trial.

In the first step, the participants will be grouped by the physician or psychotherapist into a control group (participants without mental disorders) or a case group (participants with mental disorders). All participants will provide written informed consent after being given detailed information by the treating therapist or physician. The original forms will be stored in a closed cabinet, but the participants will receive a copy. Second, they will receive a pseudonymized label for the blinded inhouse-rater to work with the questionnaires, and for the data center for the speech-analysis. Neither the rater nor the data center will know the name and diagnosis of the participant. Data security and availability will be ensured every time, according to the European Union (EU) rules [29]. The participants’ data will be stored in a MySQL-Database. Within the project database, identifying data will be stored separately from the collected data, with only project staff with specifically conferred access rights able to access the identifying data. It is envisioned that the distribution of participants will correspond to the clinical distribution in the Neuropsychiatric Center with different degrees of severity of mental disorders (about 25% mild, about 50% moderate, about 25% severe). This should be checked by the study nurse every 2 weeks.

For documentation purposes, the presence or absence (in the case of neurological outpatients) of any psychiatric diagnosis will be screened using the PHQ-D [30]. Personality traits will then be measured with the Big 5 Test [23]. In the case of ADHD, we added a Visual Analogue Scale (ADHD-VAS) to identify the three main affective states (impulsivity, inattention, and hyperactivity). This will be done at baseline only.

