### Statistical Methods

It should be possible for the study team to evaluate the efficacy and effectiveness of the raw data from the linguistic analysis in correlation with the clinical data collected with the questionnaires. All statistical tests will be two-tailed and will be considered statistically significant at *P*<.05. A sample size of 166 subjects was calculated (effect size medium=0.30; alpha=0.05; 1–beta=0.95), and considering a drop-out rate of 15%, a total sample size of 190 patients was determined. 

Statistical analysis will be performed with R version 3.5.3 (The R Project, Vienna, Austria), and epidemiological data will be evaluated. Continuous variables will be described with the mean, standard deviation, median, minimum, maximum, and the 25th and 75th percentiles. Categorical variables will be described with percentages and absolute frequencies. The differences in continuous variables between the two groups will be evaluated with the Kruskal-Wallis test, followed by the Dunn multiple comparison test. The differences between the two diagnostic groups (psychiatric versus neurological diagnosis) for normally distributed data will be evaluated with a one-way analysis of variance (ANOVA), followed by the Newman-Keuls multiple comparison test. The normality of the distribution will be evaluated with the Kolmogorov-Smirnov test. Any correlation between the variables under evaluation will be assessed by the Spearman r correlation. To compare qualitative data, we will use the Chi-square test with the Yates correction or the Fisher exact test. Lastly, the variables will be grouped to their diagnostic groups according to the 10th edition of the International Statistical Classification of Diseases and Related Health Problems or the fifth edition of the Diagnostic and Statistical Manual of Mental Disorders, and a confirmative factor analysis will be done comparing these groups with the prosodic parameters.

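### The two-group ANOVA pools one variance and the plan checks only normality, so its P<.05 may not be a 5% test if spread and group size both differ; Welch's test removes the dependence at almost no cost

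*Protocol article*

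**What the plan says.** The protocol article's Statistical Methods section sets out two group comparisons. First, "The differences in continuous variables between the two groups will be evaluated with the Kruskal-Wallis test", with Dunn's procedure afterwards. Second, for psychiatric versus neurological diagnosis, differences "for normally distributed data will be evaluated with a one-way analysis of variance (ANOVA"), with Newman-Keuls afterwards. Normality is to be assessed by Kolmogorov-Smirnov; no other assumption is mentioned. The significance rule is general: "All statistical tests will be two-tailed and will be considered statistically significant at" P<.05.

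Under Study Design and Data Protection, the treating physician or psychotherapist assigns each participant to the control group (no mental disorder) or the case group (mental disorder). The same section indicates that the participants without a psychiatric diagnosis are the neurological outpatients, so I take the diagnostic contrast and the case-control contrast to be essentially the same split. Participants are expected to mirror the clinic, "with different degrees of severity of mental disorders (about 25% mild, about 50% moderate, about 25% severe"). No case:control ratio is given. The Results section reports totals only.

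**The concern.** A one-way ANOVA in its usual form estimates a single variance from both groups. A normality check does not protect it against unequal spread. When the groups differ in both variance and size, the pooled standard error is wrong, and the true error rate moves away from the nominal 5%.

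The design gives some reason to expect unequal spread. A variable that follows severity, which is what the study hopes to find, would vary more in a group mixing mild, moderate and severe cases than in a group with no mental disorder. Nothing in the article makes equal group sizes likely, and equal sizes are what would keep ANOVA near 5% despite unequal spread.

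What is at stake is the reading of the group contrasts, which serve the second hypothesis (distinguishing diagnostic syndromes). A test that runs below 5% misses real differences; one that runs above 5% declares too many.

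**Working it through.** **Inputs from the article.** Nominal alpha 0.05, two-tailed ("effect size medium=0.30; alpha=0.05"). Total N = 166 ("A sample size of 166 subjects was calculated"), used here only as the number analysed; its derivation is not examined. Severity mix 25/50/25%.

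**Assumed inputs, because the article gives none.** Splits of cases:controls 111:55 (about 2:1) and 124:42 (about 3:1), with 83:83 for reference; SD ratio 1.3 or 1.5 in either direction.

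**Is an SD ratio of 1.3 to 1.5 plausible?** Suppose a variable shifts by d within-level SDs per severity step, and the SD within each level equals that of controls. Scoring mild, moderate and severe as -1, 0, 1 with weights 0.25, 0.50, 0.25 gives a variance of 0.5, so the case SD is √(1 + 0.5d²): 1.22 at d = 1 and 1.46 at d = 1.5. The ratios are not extreme, but d is assumed.

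**Formula.** With equal means, group sizes n1, n2 and SDs s1, s2:

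- true variance of the mean difference: V = s1²/n1 + s2²/n2
- variance ANOVA expects: P = sp²(1/n1 + 1/n2), with sp² = [(n1−1)s1² + (n2−1)s2²]/(N−2)
- actual alpha ≈ 2[1 − Φ(1.96/√(V/P))]

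**Nominal figure first.** With s1 = s2, V = P and alpha = 0.05 at any split. Simulation (20,000 replicates, normal data) agrees: 0.049 to 0.052 for splits from 83:83 to 149:17. With n1 = n2, V = P again; simulated ANOVA alpha at 83:83 and SD ratio 2 was 0.049.

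**Worked case, 124:42, cases SD 1.5, controls SD 1.** V = 2.25/124 + 1/42 = 0.04195. sp² = (123×2.25 + 41×1)/164 = 1.9375. P = 1.9375×(1/124 + 1/42) = 0.06176. V/P = 0.679, so alpha = 0.0174.

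**Same split, controls SD 1.5, cases SD 1.** V = 1/124 + 2.25/42 = 0.06164. sp² = (123×1 + 41×2.25)/164 = 1.3125. P = 0.04183. V/P = 1.473, so alpha = 0.1064.

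| Split (cases:controls) | More variable group | SD ratio | V/P | Actual alpha |
|---|---|---|---|---|
| 111:55 | cases | 1.3 | 0.840 | 0.0325 |
| 111:55 | cases | 1.5 | 0.769 | 0.0254 |
| 124:42 | cases | 1.3 | 0.774 | 0.0259 |
| 124:42 | cases | 1.5 | 0.679 | 0.0174 |
| 111:55 | controls | 1.3 | 1.191 | 0.0725 |
| 111:55 | controls | 1.5 | 1.301 | 0.0857 |
| 124:42 | controls | 1.3 | 1.292 | 0.0847 |
| 124:42 | controls | 1.5 | 1.473 | 0.1064 |

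Simulation at SD ratio 1.5 gives 0.027 and 0.019 (cases more variable; 2:1, 3:1) and 0.088 and 0.103 (controls more variable), in line with the formula. Because V/P depends almost entirely on the split and the SD ratio, recruiting more participants does not remove the effect.

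**Welch.** Across all simulated splits (50% to 90% cases) and SD ratios (0.5 to 2), Welch's test stayed at 0.046 to 0.053.

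**The case against.** The strongest reply is that both conditions are assumed. The article states no group counts and no SD for any speech parameter. The sentence about mirroring the clinic concerns severity, not the number of controls, and neurological controls may be just as heterogeneous as cases. This stands: a reader might infer that the groups are unbalanced and that P<.05 is therefore not a 5% test, but the document supports only the conditional statement.

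A reader might also infer an excess of false positives. The design argument points the other way. If the severity-mixed cases are both the larger and the more variable group, the test is conservative and the cost is power. Inflation needs the smaller group to be the more variable one, and the article gives no reason to expect that. Nor does it say that the contrast is repeated for each of the more than 200 speech parameters.

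It is tempting to extend the criticism to Kruskal-Wallis. At 124:42 and SD ratio 1.5 it rejects 0.030 or 0.078 of the time when only spread differs, but that counts as error only if it is read as a test of location. It holds its size under its own null of identical distributions, and the article speaks only of differences. Replacing it would be a preference.

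Finally, the article does not say which variance form of ANOVA is meant, and a fuller plan might. That is fair in part, though Newman-Keuls in its standard form uses a pooled error and so points to the pooled version. The primary objective, comparing speech parameters with questionnaires, is served by Spearman correlation and is untouched.

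**Conclusion.** The point holds as a conditional one. The named procedure is sensitive to unequal spread combined with unequal group sizes, and the stated check covers neither. Under the assumed 2:1 to 3:1 splits (more cases than controls) and SD ratios of 1.3 to 1.5, actual alpha is about 0.017 to 0.033 if cases are more variable and about 0.07 to 0.11 if controls are. If either the SDs or the group sizes are equal, there is no problem. The splits and SD ratios are assumptions throughout. This is a minor, inexpensive improvement to a secondary analysis, not a demonstrated error.

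**What to change.** In Statistical Methods, replace the one-way ANOVA for psychiatric versus neurological diagnosis with Welch's unequal-variance test, and report the mean difference with its 95% confidence interval. Delete the Newman-Keuls step: two groups yield a single comparison, so there is nothing to follow up. Keep Kruskal-Wallis if wanted, adding that a significant result means the distributions differ, not necessarily their location.

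The cost is one sentence and a different function call in R. The power loss when variances are equal is negligible. For example, at 124:42 with equal SDs the Welch degrees of freedom are (1/124 + 1/42)² / [(1/124)²/123 + (1/42)²/41] ≈ 71 instead of 164, which moves the critical t from about 1.975 to 1.994, or 1%.

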### Research Objectives

The primary objective of this study is to evaluate the measurements of the mental state of the participants by comparing the analysis of noncontent speech parameters to the results of several psychological questionnaires (Symptom Checklist-90 [SCL-90], the Patient Health Questionnaire [PHQ], and the Big 5 Test). We hypothesized that the emotional state of mind, the behavioral patterns, the well-being, and some of the personality traits of the participants could be identified using the prosodic analysis algorithm. A second hypothesis is that the diagnosis could be confirmed by the application of the analysis program, and a distinction can be made between different psychopathologically-defined syndromes.

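### The voice-questionnaire correlations and group comparisons are specified without adjustment for sex or age, so either could reflect demographics instead of mental state

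*Protocol article*

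**What the plan says.** The Research Objectives section states the primary aim as "comparing the analysis of noncontent speech parameters to the results of several psychological questionnaires" (SCL-90, PHQ and Big 5). The Statistical Methods section then names the tests:

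- Association: "Any correlation between the variables under evaluation will be assessed by the Spearman r correlation".
- Continuous variables by group: "The differences in continuous variables between the two groups will be evaluated with the Kruskal-Wallis test, followed by the Dunn multiple comparison test".
- Normally distributed data, psychiatric versus neurological diagnosis: "will be evaluated with a one-way analysis of variance (ANOVA), followed by the Newman-Keuls multiple comparison test".
- Qualitative data: "we will use the Chi-square test with the Yates correction or the Fisher exact test".
- A last step by diagnostic group: "a confirmative factor analysis will be done comparing these groups with the prosodic parameters".

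No covariate is named for any of them, and no partial correlation, regression, stratification or matching is stated. Under Study Design and Data Protection, the treating clinician assigns participants to case or control according to whether they have a mental disorder. The same section and Statistical Methods indicate that the controls are neurological outpatients. Age appears only as the 18-65 eligibility range in Textbox 1. Sex is not mentioned anywhere in the article.

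**The concern.** A bivariate rank correlation does not distinguish a voice parameter that moves with distress from one that merely differs between men and women, or between younger and older people, when the questionnaire score differs along the same line. The one-factor group tests have the same weakness: if the two diagnostic groups differ in sex or age mix, a difference in a voice parameter may come from that mix. Randomisation would guard against this in the group contrast, and matching would help, but the design has no randomisation and states no matching.

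At stake is the interpretation of the main result. A significant coefficient from the analysis as written would not by itself show that speech reflects mental state.

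**Working it through.** **Plan's own figure.** The article gives no estimate of confounding, so there is none to reproduce. Only its n=166 and two-sided alpha of 0.05 are used below. (Fisher z for r=0.30 at 95% power gives 139, not 166. That is a separate matter, and nothing here depends on it.)

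**Assumed inputs, not in the documents.** Half the sample are women. The questionnaire scale differs by d1 = 0.3 or 0.5 SD between the sexes, and the voice parameter by d2 = 0.3 to 3 SD (SDs are within sex). Within each sex, voice and score are unrelated.

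**Formula.** With p the proportion of women, the correlation in the whole sample is

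r = p(1-p)·d1·d2 / sqrt[(1 + p(1-p)·d1²)(1 + p(1-p)·d2²)].

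Example, p=0.5, d1=0.3, d2=2: r = 0.25×0.3×2 / sqrt(1.0225×2) = 0.15/1.430 = 0.105.

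**Rejection rate.** By Fisher z, the test statistic is centred at m = atanh(r)·sqrt(166-3) = atanh(r)×12.77. The rate is P(Z > 1.96-m) + P(Z < -1.96-m). For the example, m = 1.34 and the rate is 27%. The critical |r| at n=166 is about 0.152.

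| Scale difference d1 | Voice difference d2 | Spurious r | Declared significant |
|---|---|---|---|
| 0.3 | 0.3 | 0.022 | 6% |
| 0.3 | 0.5 | 0.036 | 7% |
| 0.3 | 1 | 0.066 | 14% |
| 0.3 | 2 | 0.105 | 27% |
| 0.3 | 3 | 0.123 | 35% |
| 0.5 | 0.3 | 0.036 | 7% |
| 0.5 | 1 | 0.108 | 28% |
| 0.5 | 2 | 0.171 | 60% |
| 0.5 | 3 | 0.202 | 74% |

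**Check by simulation.** This used 4,000 runs per setting at n=166, a 50:50 binary confounder and no voice-score link within its levels. With confounder correlations of 0.3 (voice) and 0.1 (score), plain Spearman rejected in 6% of runs; with 0.5 and 0.3, in 49%. Across all settings tried, Spearman partialled for the confounder rejected in 4.6% to 5.5%.

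**Cost of adjusting for two covariates.** Power at r=0.30 and n=166 is Φ(atanh(0.30)·sqrt(166-3-k) - 1.96), with atanh(0.30)=0.3095. For k=0: Φ(0.3095×12.77 - 1.96) = 97.7%. For k=2: Φ(0.3095×12.69 - 1.96) = 97.5%.

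**Group comparisons.** The bias depends on how far the two groups differ in sex and age. The article gives no baseline data, so I put no figure on it.

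**The case against.** The best defence is that this is a condensed article and the analysis plan is not shown. Choice of covariates is often left to that plan, and naming Spearman does not exclude a partial or stratified version. This stands in part: the article nowhere says that correlations are pooled over cases and controls, or labels Spearman as the primary analysis. But it lists a test for each kind of comparison, all bivariate or one-factor, and one-way ANOVA and Kruskal-Wallis as named have no place for a covariate. Followed as written, the plan leaves the main question unadjusted.

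A second objection is that the size rests on assumptions. That stands. The article describes more than 200 proprietary parameters and does not say how many differ by sex, or whether any are normalised for the speaker. At the weak end the inflation is negligible.

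Three stronger readings are tempting and not supported:

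- A reader might infer that the two groups do differ in sex and age. The documents give no baseline data, so this is a risk and not a fact.
- A reader might infer that neurological disease in the controls creates a spurious correlation. If SCL-90 differed by 1 SD and a voice parameter by 0.5 SD between equal groups, the formula gives r=0.108 and 28% rejection; at 0.2 SD it gives r=0.044 and 9%. Neither difference is documented. The Abstract excludes neurological speech or language disorders, and Textbox 1 rules out dementia and recent cerebrovascular events. Textbox 1 does not repeat the Abstract's exclusion, but the safeguard cannot be ignored.
- A reader might infer that the primary correlation should also be adjusted for case/control group. Group is defined by presence of a mental disorder, so it carries part of the signal that the study seeks, including under its second hypothesis. Adjusting for it could remove real association and would change the quantity estimated.

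**Conclusion.** The point holds for sex and age. The article fixes unadjusted methods for its central question in a non-randomised sample with no matching stated, so a significant result could not be attributed to mental state on that analysis alone. The assumed range of 6% to 74% false positives shows what could happen under weak to strong confounding by sex. It is not an estimate for this study, and no single value in it can be preferred on the documents. The case for changing the plan rests on the structure of the analysis and on the small cost of adjustment, not on any one rate. It is a recommended improvement to the analysis. It does not show that the study's results will be wrong.

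**What to change.** In Statistical Methods:

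1. Report the voice-questionnaire correlations as partial Spearman (rank regression) adjusted for sex and age, with unadjusted Spearman as secondary.
2. Compare the groups by rank or linear regression on group, sex and age in place of the one-factor tests.
3. Show the correlations within cases and within controls as a supporting analysis beside the pooled one, without making group adjustment the primary measure.

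The cost is wording and about two degrees of freedom (power 97.7% to 97.5% at r=0.30, n=166). Sex and age must be in the dataset. Age is an eligibility criterion, so it should be available; sex is not mentioned, so its recording is an assumption to confirm. The Results section places final calculations after the article's reporting date, so at that date the change could still be made before analysis.

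One limit remains: because the controls are the neurological patients, no adjustment can separate neurological from psychiatric effects in the group contrast, and the report should say so.

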#### Speech Analysis

The audio that will be sent to the server will be analyzed using VoiceSense proprietary speech analysis. This analysis produces raw data of over 200 prosodic parameters for each call. The raw data parameters will be sent back to the research center for the statistical analysis, with a sampling frequency of 8 kilohertz.

VoiceSense speech analysis focuses on speech prosody, the noncontent aspects of the speech, such as intonation, pace, stressing, and other aspects. The analysis is language independent and has been tested successfully in many languages (different European languages, different Asian languages, etc). The analysis was validated versus various personality tools, such as Big 5 [23], Holland [24], Hogan [25], WPI [26], and linked speech patterns (clusters of the raw speech parameters) with the personality scales as measured by these tools. The analysis is based on several granted patents regarding measurement of emotional state [27] and behavioral tendencies [28] through speech analysis. This proprietary speech anal ysis is the basis for commercial products in the fields of enterprise, big data analytics, customer analytics, human resources, and others.

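### The only analysis by ICD-10/DSM-5 group is a confirmatory factor analysis, which does not measure how well speech identifies a diagnosis and, on all 200 or more parameters, has no standard fit test at the planned size

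*Protocol article*

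**What the plan says.** Research Objectives puts forward, as the second hypothesis, that "the diagnosis could be confirmed by the application of the analysis program, and a distinction can be made between different psychopathologically-defined syndromes".

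Speech Analysis describes the data available for this: "This analysis produces raw data of over 200 prosodic parameters for each call". It adds that "The raw data parameters will be sent back to the research center for the statistical analysis", and states no reduction step for this study.

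Statistical Methods gives the planned size: "A sample size of 166 subjects was calculated (effect size medium=0.30; alpha=0.05; 1–beta=0.95"), and then "considering a drop-out rate of 15%, a total sample size of 190 patients was determined". It lists Kruskal-Wallis with Dunn comparisons between the two study groups, one-way ANOVA with Newman-Keuls comparisons for psychiatric versus neurological diagnosis, and Spearman correlations. The last item assigns the variables to ICD-10 or DSM-5 diagnostic groups, after which "a confirmative factor analysis will be done comparing these groups with the prosodic parameters". No other analysis is planned at the level of ICD-10/DSM-5 groups.

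**The concern.** Confirming a diagnosis and separating syndromes are questions about assigning people to classes. The answer is an error rate or a discrimination measure against a reference diagnosis. Confirmatory factor analysis asks something else: whether a loading pattern fixed in advance reproduces the covariances among the measured parameters. A good fit would not show that speech identifies depression or ADHD. A poor fit would not show that it cannot.

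The second doubt is scale. The number of parameters exceeds the planned number of subjects, and standard maximum-likelihood fit testing does not tolerate that.

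At stake is one of the two stated hypotheses. If the planned method cannot answer it, an improvised analysis may take its place. Picking parameters and judging accuracy on the same patients would then overstate what the tool can do.

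**Working it through.** **1. The plan's own sample size.** The article does not say which test the 166 was computed for. With its inputs and "All statistical tests will be two-tailed", a correlation of 0.30 by Fisher's z needs

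n = [(1.960 + 1.645) / atanh(0.30)]² + 3 = (3.605 / 0.3095)² + 3 ≈ 138.7, so 139.

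A chi-square test with w=0.30 and 1 df needs 145, and a two-group ANOVA with f=0.30 needs 148. Of the variants tried, only those with an unstated division by a rank-test efficiency of 0.864 came close (168 and 169). The 190 is 166 × 1.15 = 190.9, rounded down. The inputs are a single effect size, alpha and power, with no number of parameters or factor model among them. So 166 cannot be taken as a size chosen for a factor analysis. Whether 166 and 190 are right for other purposes is a separate matter.

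**2. Hypothesis against method.**

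| | Second hypothesis | Confirmatory factor analysis |
|---|---|---|
| Question | Does speech identify the diagnosis or syndrome? | Does a prespecified loading structure reproduce the covariances? |
| Role of diagnosis | Observed class to be predicted | None in the basic model; grouping variable or covariate in extensions |
| Result | Sensitivity, specificity, AUC | Loadings, fit statistics; in extensions, differences in latent means |

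A difference in latent means between groups is compatible with heavy overlap between individuals, so even the extensions give no error rate for a diagnosis.

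**3. Rank of the covariance matrix.** Take p=200, the lower bound in Speech Analysis. The sample covariance matrix S satisfies rank(S) ≤ min(p, N−1).

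| N | Source | Maximum rank | Full rank (200)? |
|---|---|---|---|
| 62 | reached study end (Results) | 61 | no |
| 161 | complete at time point one (Results) | 160 | no |
| 166 | planned | 165 | no |
| 190 | planned with dropout | 189 | no |
| 254 | enrolled (Results) | 200 | yes, only if all had complete data |

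At least 201 complete cases are needed. The maximum-likelihood discrepancy is

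F = log|Σ| + tr(SΣ⁻¹) − log|S| − p, with test statistic (N−1)F.

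When S is singular, |S| = 0 and log|S| does not exist. The chi-square and the indices built on it are then undefined.

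**4. Parameter count.** With each speech parameter loading on one of m correlated factors, the free parameters number 2p + m(m−1)/2. For m=1 that is 400, for m=5 it is 410, and for m=9 it is 436. The article gives no m, so this range is an assumption. At N=166 it leaves 166/400 = 0.42 to 166/436 = 0.38 subjects per parameter.

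**5. Is estimation itself impossible?** No. One data set was simulated with p=200, N=166 and five factors, and the correct model was fitted by EM. It gave a mean loading of 0.603 against a true 0.60, with all residual variances positive. What fails is the fit test.

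**6. Would more subjects rescue the fit test?** Not at the enrolled number. At N=254 the degrees of freedom are 20,100 − 410 = 19,690. The test rejected the correct model in 20 of 20 simulated data sets, with statistic/df about 1.49 in the last.

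**7. Illustration of an unvalidated substitute.** This is not a planned analysis. Choose the best 10 of 200 pure-noise parameters and judge AUC on the same 166 people; the true value is 0.50. The group sizes and correlations below are assumptions.

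| Assumed setting | Median apparent AUC |
|---|---|
| 83 vs 83, independent parameters | 0.80 |
| 125 vs 41, independent parameters | 0.84 |
| 83 vs 83, blocks of 10, correlation 0.5 | 0.76 |
| 83 vs 83, blocks of 20, correlation 0.5 | 0.73 |
| 83 vs 83, blocks of 20, correlation 0.8 | 0.67 |

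**The case against.** The best defence is that this is a condensed article. It does not say that every raw parameter enters one maximum-likelihood model. Estimator, factor model and parameter reduction may be set out in a fuller document. Speech Analysis shows that the vendor has worked with groupings before: earlier validation "linked speech patterns (clusters of the raw speech parameters) with the personality scales as measured by these tools". Multi-group and MIMIC models do compare observed groups. The wording could also mean that parameters are assigned to diagnosis-defined factors. The article never names the factor analysis as the test of the second hypothesis, and Kruskal-Wallis and ANOVA also bear on group differences. The primary objective, agreement with questionnaires, is served by the Spearman correlations.

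Much of this stands. The singularity argument is conditional on all parameters entering one standard fit. Linking the factor analysis to the second hypothesis is an inference, though a strong one, because nothing else works at syndrome level. The clusters belong to the vendor's past validation and are not a step of this study, but a reduced set remains possible. The lack of stated sensitivity or specificity would be no finding on its own, since an article may leave that to an analysis plan.

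What the defence does not reach is the choice of method. The article names one, and under every reading, including diagnosis-defined factors, it describes how parameters covary or how latent means differ. It does not describe how well a patient's diagnosis is recovered. Kruskal-Wallis and ANOVA compare two broad groups and say nothing about identifying individual syndromes.

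**Conclusion.** The point holds in two parts. First, without any assumption about the model: the only analysis by ICD-10/DSM-5 group does not measure what the second hypothesis claims. Second, on the condition that all 200 or more raw parameters enter one standard maximum-likelihood model: the covariance matrix is singular at the planned size (rank at most 165 of 200 at N=166, 189 of 200 at N=190), so the usual fit test and its indices are undefined.

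Three stronger conclusions are tempting and are not supported:

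- A reader might infer that the factor analysis cannot be estimated at all. EM gave sensible estimates at p=200 and N=166, and the article does not exclude other estimators or fewer parameters.
- A reader might infer that nothing in the plan bears on the second hypothesis. The two-group tests can support or contradict a broad difference in speech, which is part of it.
- A reader might infer that the study will report an AUC of about 0.80 by chance. No such selection is planned. The apparent AUC runs from about 0.67 to 0.84 depending on assumed group sizes and correlation, and serves only as a warning about unvalidated substitutes.

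The primary objective is not affected.

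**What to change.** In Statistical Methods, replace the sentence on the factor analysis, as the test of the second hypothesis, with a classification analysis:

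- **Model.** A penalised classifier of the clinician diagnosis on the prosodic parameters. Elastic-net logistic regression for case versus control is one acceptable choice, with penalised multinomial regression for syndromes. Fix in advance how many participants a syndrome needs to be included.
- **Validation.** Carry out all parameter selection and tuning inside cross-validation split by participant. Recordings are made in one to three sessions per person, so all sessions of one participant must fall in the same fold.
- **Reporting.** Out-of-sample AUC, sensitivity and specificity against the clinician diagnosis, with confidence intervals, for example by bootstrap over participants.
- **Interpretation.** A lower AUC bound above 0.5 is evidence of discrimination only. Set a higher value in advance, with reasons, before claiming that a diagnosis is confirmed.

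If a factor analysis is kept for description, state the factor model, the estimator and the reduced parameter set, and do not present it as evidence of diagnostic accuracy.

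The change uses data already being collected and costs plan wording and some R programming. The downside is that out-of-sample accuracy will be lower than in-sample fit, and rare syndromes may be too small to analyse. It should be settled before the final calculations are run.
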